### Outcome measurement

Follow-up by means of routine data will cover four quarters before and after each prescribing-related PEM intervention. Each of the process-of-care measures has been used in large-scale studies using databases held at ICES.

### Proposed sample size

We wished to have adequate power to detect modest changes in the way physicians practice. Based on the median absolute effectiveness of PEMs estimated from the Grimshaw review (8%) [7], it would be important to detect 5% and 10% absolute improvements in our target behaviours. Even 5% improvements in the prevalence of evidence-based care for these common conditions will be an important achievement, with significant health benefits for many Ontarians.

In pilot data, the baseline-prescribing rate of ACE inhibitors in persons with diabetes was 36%, and the intra-class correlation for ACE inhibitor use by patients clustered within physicians was 9.2%. With an assumption that one-half of doctors work in solo practices, we ran these data testing power at a mean of three patients and ten patients per practice. Monte Carlo simulations demonstrated that a trial with 1250 practices per arm, with 10 patients per practice and an alpha of 0.05 will provide more than 98% power to detect a 10% absolute increase in the rate of ACE inhibitor use, more than 97% power to detect a 5% absolute increase, and more than 98% power to distinguish between the effects of the combined intervention and either alone, assuming the combined effect to be additive.

Because the baseline rates of the other interventions are comparable or lower (screening for retinopathy, diuretic use, aggressive blood pressure-reducing, and cholesterol-lowering therapies), and the number of patients per practitioner with these conditions is the same or higher, we will have adequate power to detect similar absolute increases for those endpoints.

Later, with the addition (see Table 1) of two groups in the second (patient reminder note) and third (theory-based outsert) replicates, a less comprehensive, but approximate simulation suggested that the impact on power would be minor and would most certainly be greater than the often used target of 80%. The research opportunity that this modification presented was judged to outweigh the likely loss of power. Therefore, we maintained 1,250 practices in the two groups that did not receive an outsert with ***informed***, and assigned 625 practices to each of the four groups who were sent an outsert.

### Recruitment, compliance, loss to follow-up, and drop-out

Practitioners may of course decide to ignore the PEMs or never open the envelope containing ***informed***. We will not know what practitioners will do with the intervention, a normal feature of the pragmatic trial philosophy that tests interventions under real-world conditions. ***informed ***will be mailed in the usual fashion to all identified practitioners. Any practitioners who subsequently remove themselves from the mailing list for ***informed ***will be analysed in the allocated arm on an intention-to-treat basis.

While the unit of analysis is the physician, loss of patients is important to detect in order to maintain accurate denominators for the determination of outcome rates. Patients may be lost due to removal from the system (death or out-migration), or change of provider. The former will be detected in the RPDB, the latter by a plurality rule for prescriptions. For the baseline analysis (pre-intervention period), the initially assigned patients for each physician will be used. For each of the succeeding observation periods (three pre- and four post-intervention), initial patients will be confirmed by eliminating patients no longer eligible according to the RPDB, and ensuring that assigned patients are still being cared for by the study physician through a requirement that the study physician must have written the plurality of the patient's prescriptions in that period.

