### Allocating participants to trial groups

Trials of interventions aimed at changing clinical practices must be randomized at the level at which they are directed – that is, at the level of the doctor, not his or her patients. In group practices, however, doctors may well share information. To prevent contamination, randomization must take place at the level of the group rather than the individual practitioner. A group practice is defined here as all primary care physicians who share a common street address, or who share a common office number in a multi-office building. The eligible Ontario primary care doctors will be fee-for-service family physicians (FPs) and general practitioners (GPs) (Ontario Health Insurance Program [OHIP] billing code 00).

These practitioners will be identified from the health care providers database held at ICES. They will be verified to be in active practice. In order to enable prescribing outcomes to be measured, we will ensure that they have an adequate volume of seniors among their patients by requiring that they write at least 100 prescriptions appearing in the ODB (Ontario Drug Benefit Program) database in the year prior to enrollment. The physician identifier obtained from these ODB claims first will be linked to the physician's College of Physicians and Surgeons of Ontario (CPSO) number at ICES. Addresses of practitioners will be obtained by hand-linking the CPSO number to the CPSO database, which is publicly available on the Internet. The CPSO website can be queried by CPSO number and will supply physician name and practice address.

All FPs and some GPs are already on the ***informed ***mailing list. Those who are not currently on the list will be added for the three intervention issues of ***informed***. This list will be sorted by addresses of practitioners into practices, in order to prevent practitioners with the same address, who may share administrative staff or communicate readily with each other, from being randomized to different groups (i.e., to reduce contamination). Using a computer-generated sequence of random numbers, the practices will then be randomized to one of the intervention groups. For each of the three replicates, we will re-randomize physician practices to one of the intervention groups.

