### Analyses

We hypothesize that the active intervention arms will be superior to control, similarly effective to each other, and with some additive effect when both are delivered. Analyses will be concentrated on this hypothesis.

The study employs a cluster randomized design. The analysis will be carried out using multi-level, hierarchical, logistic regression models, with the trial arm being a physician-level variable, and the prescribing (or screening) outcome a patient-level variable. These models account for clustering of patients within practices, and the consequent lack of independence of prescribing outcomes within a given physician's place of practice [55]. No place-of-practice characteristics, aside from the arm of the trial and baseline adherence to guidelines, will be entered into the model in the primary analysis. With so many physicians randomized to each arm, we anticipate that measured and unmeasured physician factors that might affect the outcome will be equally distributed between the arms. Moreover, including more place-of-practice characteristics in the model would reduce the statistical power to detect the primary outcome.

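### Practices are randomised, but the protocol gives conflicting statements on whether the physician or the practice is the level of analysis

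*Protocol article*

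**What the plan says.** All places are in the protocol article.

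- **Allocating participants to trial groups.** To limit contamination, "randomization must take place at the level of the group rather than the individual practitioner". A group practice is defined by a shared street address or office number, and "the practices will then be randomized to one of the intervention groups".
- **Recruitment, compliance, loss to follow-up, and drop-out.** "While the unit of analysis is the physician, loss of patients is important to detect". The follow-up rules there assign and confirm patients by physician.
- **Analyses, model description.** Multilevel logistic models are planned "with the trial arm being a physician-level variable, and the prescribing (or screening) outcome a patient-level variable". The paragraph later argues for balance from the large number of physicians randomised to each arm.
- **Analyses, next two sentences.** "These models account for clustering of patients within practices, and the consequent lack of independence of prescribing outcomes within a given physician's place of practice". Then: "No place-of-practice characteristics, aside from the arm of the trial and baseline adherence to guidelines, will be entered into the model". Here arm is counted among the characteristics of the practice.
- **Proposed sample size.** Clusters are counted as practices (1250 per arm, 10 patients per practice) and half of doctors are assumed to be solo. The only ICC is at physician level: "the intra-class correlation for ACE inhibitor use by patients clustered within physicians was 9.2" per cent.
- **Discussion.** Randomising by place of practice is said to avoid unit of analysis error.

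**The concern.** Allocation is by practice, so all physicians at one address share an arm. Inference on arm contrasts must allow for correlation between those physicians. A model of patients within physicians, without a practice effect, does not, and it overstates the independent information from group practices. On the protocol's own assumption these hold half of the doctors.

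The protocol can be read either way. An analyst who takes the unit-of-analysis statement and the physician-level label for arm at face value would cluster on physician. One who takes the next sentence of Analyses would cluster on practice. Randomising by practice does not by itself avoid unit of analysis error, because the analysis has to respect that level too. The Background and Discussion criticise earlier trials for this very error. At stake is the type I error of every arm contrast in all three replicates.

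**Working it through.** **1. The stated power.** Inputs from Proposed sample size: baseline 36%, ICC 0.092, 1250 practices per arm, alpha 0.05 (taken as two-sided). Design effect = 1 + (m − 1) × ICC.

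- m = 10: 1 + 9 × 0.092 = 1.828, so effective n per arm = 12,500 / 1.828 = 6838. Power is 99.997% for 36% v 41%, 99.996% for 41% v 46% (combined v single), and about 100% for 36% v 46%.
- m = 3: design effect 1.184, effective n 3167. Power is 98.3%, 98.0% and about 100%.

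The stated lower bounds (above 97% and 98%) are reproduced. With the practice as cluster, m = 10 and a practice ICC of 0.20 or 0.30, power for 36% v 41% is still 99.8% or 98.8%.

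**2. Error rate if the model clustered on physician only.** Let half of doctors be solo (protocol) and the other half work in groups of g (assumed). Let a share s of the 0.092 lie at practice level (assumed), and let n be the patients per physician.

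- Mean practice size as seen by a physician: k = 0.5 + 0.5g.
- Correlation between the mean outcomes of two physicians in one practice: r = s × 0.092 / (0.092 + 0.908/n).
- Factor by which the variance is understated: F = 1 + (k − 1) × r.
- Actual two-sided error: 2 × [1 − Φ(1.96/√F)].

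There are 4 × 1250 = 5000 practices, with 1/(0.5 + 0.5/g) physicians per practice on average. Two values of n are used: one from 10 patients per practice (the sample-size input), and one from 280,000/5000 = 56 per practice (replicate 1, Table 2).

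| g | s | n at 10 per practice | F | error | n at 56 per practice | F | error |
|---|---|---|---|---|---|---|---|
| 2 | 0.3 | 7.5 | 1.06 | 5.8% | 42.0 | 1.12 | 6.4% |
| 3 | 0.3 | 6.7 | 1.12 | 6.4% | 37.3 | 1.24 | 7.8% |
| 4 | 0.5 | 6.3 | 1.29 | 8.5% | 35.0 | 1.59 | 12.0% |
| 6 | 0.7 | 5.8 | 1.65 | 12.7% | 32.7 | 2.34 | 20.0% |

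Worked case, g = 4, s = 0.5, n = 35: k = 2.5; r = 0.046 / (0.092 + 0.0259) = 0.390; F = 1 + 1.5 × 0.390 = 1.59; error 12.0%.

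At 10 patients per physician rather than per practice, the first and last rows become 5.9% and 15.3%.

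**3. Simulation under no effect.** Set-up: 500 practices per arm, half of doctors solo and half in groups of four, 10 patients per physician, 2000 runs. With standard errors clustered on physician, the rejection rate was 5.1%, 7.3%, 10.0% and 14.0% at practice-level ICCs of 0, 0.03, 0.046 and 0.092. With clustering on practice it was 5.0 to 5.5% throughout.

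**The case against.** The strongest reply is that the plan already states the right model. The sentence after the physician-level label commits to clustering within practices, the next one treats arm as a practice characteristic, and the sample size counts practices. The unit-of-analysis remark is a subordinate clause about tracking denominators that contrasts physician with patient and specifies no model. The label for arm does not set the level of the random effect: arm is constant within a practice, so with a practice effect the standard error is right.

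Most of this stands. A reader might infer that the trial's standard errors will be too small, or that a unit of analysis error has been shown. The documents do not support that, because it would require following the physician-level statements against the explicit sentence on practice clustering. A reader might also cite the within-physician ICC as a cause of small standard errors. It is not one: it enters the power calculation only, and applied to 10 patients per practice it is conservative if the practice ICC is no larger.

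What does not fall away is the contradiction. One section states a unit of analysis that differs from the unit of randomisation, and the Analyses section uses both levels within one paragraph. This is not a detail left to an analysis plan, since the article itself fixes the level in two incompatible ways.

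**Conclusion.** The point holds as an inconsistency with a conditional consequence, and its severity is moderate. If the physician-level statements governed the analysis, a nominal 5% error would be about 6 to 13% at 10 patients per practice, and about 6 to 20% in replicate 1 at the expected patient numbers. If the practice-clustering sentence governs, error is near 5%.

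The ranges rest on assumed group sizes (2 to 6) and an assumed practice share of the ICC (30 to 70%), neither of which the protocol gives. The 20% figure needs the top of both ranges together with the larger patient number. With no correlation between physicians of a practice there is no inflation. The stated power is not in question.

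**What to change.** Reconcile the section on recruitment and loss to follow-up with the Analyses section:

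- Name the practice as unit of randomisation and of inference. Keep the physician only as the level at which patients are attributed and tracked.
- Describe arm as a practice-level variable, and refer to practices, not physicians, as randomised to each arm.
- State that the primary model includes a practice random intercept, with physician nested within practice if wanted.
- Keep the 9.2% ICC labelled as physician-level where it is used for power.

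The cost is a few lines of wording and one random effect. Compared with a physician-only model, intervals widen by √F, the part that such a model would wrongly leave out. No change to the sample size is needed.

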The relevant patients for each practice are defined as any patient attending that practice who meets study entry criteria. For each of the gaps, we are using a different algorithm to identify relevant patients (see Table 2). A patient may be counted multiple times, as they are free to attend more than one primary care practice. This approach is conservative, and gives all physicians "credit" for appropriate prescribing or referral decisions made by any of the physicians who saw that patient during the study period. In a sensitivity analysis, we will use a more rigorous rule for defining physician-patient relationships, whereby patients will be assigned only to the primary care provider with whom they had a plurality of their visits. In a tie, the patient will be assigned to the primary care physician who wrote the greatest number of their prescriptions during the study period. Patients who still cannot be unambiguously assigned will be allocated randomly to one of the practitioners who have written prescriptions for them during the study period.

**Table 2 T2:** Patient population and primary outcome for each of 3 replicates

**Replicate**	**Evidence/Practice Gap**	**Patients studied**	**Expected patient N**	**Primary Outcome**
1	Use of ACE inhibitors, blood pressure and cholesterol-reducing drugs (ABCs); each fall short of guideline targets by at least 30%	All prevalent cases of persons with diabetes, aged ≥ 65 years	280,000	% of target patients receiving an ACE inhibitor, % receiving 2 or more antihypertensive, and % receiving lipid-lowering drug
2	Retinopathy screening in incident Type 2 DM; 50% below guideline-recommended levels	All incident cases of persons with diabetes, aged >30 years	100,000	% of target patients receiving complete eye exam from optometrist or ophthalmologist
3	Use of hydrochlorothiazide (HCTZ) as initial therapy in uncomplicated hypertension; ~40% below guideline-recommended levels	All patients ≥ 65 years, newly initiated on antihypertensive therapy	30,000	% of target patients receiving a diuretic

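### The patient-denominator rule fixes a closed list before the mailing, so in replicate 3 an effect on first-line drug choice could not be observed; replicate 2 is affected to a lesser degree

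*Protocol article*

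**What the plan says.** The section on recruitment, compliance, loss to follow-up and drop-out sets the denominators.

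- At baseline: "For the baseline analysis (pre-intervention period), the initially assigned patients for each physician will be used".
- Afterwards: "For each of the succeeding observation periods (three pre- and four post-intervention), initial patients will be confirmed by eliminating patients no longer eligible".
- To stay on the list, a patient must also pass a provider check: "the study physician must have written the plurality of the patient's prescriptions in that period".

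The section on outcome measurement gives the window: "Follow-up by means of routine data will cover four quarters before and after each prescribing-related PEM intervention".

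Table 2, in the section on allocating participants, defines the three populations.

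- Replicate 1: "All prevalent cases of persons with diabetes, aged ≥ 65 years", expected N 280,000.
- Replicate 2: "All incident cases of persons with diabetes, aged >30 years", expected N 100,000.
- Replicate 3: "All patients ≥ 65 years, newly initiated on antihypertensive therapy", expected N 30,000. The stated gap is hydrochlorothiazide as the initial drug. The stated outcome is the percentage of target patients who receive a diuretic.

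The text before Table 2 takes as relevant every patient who attends a practice and meets the entry criteria, with a separate identification algorithm for each gap. That reads as open entry. The following paragraph says that prescription claims exist only for people aged 65 and older.

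**The concern.** A list that is fixed once and then only shrinks is a reasonable way to follow people with an established disease. It does not fit a population defined by a new event. The choice of a first antihypertensive is made once, when treatment starts. If the list closes before the mailing, no patient on it can have that choice changed by the mailing, and the patients in whom it could be changed are never counted.

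At stake is whether replicate 3 can answer its own question. A comparison of arms after the mailing would set side by side patients whose initial drug was chosen before any practice received a message. A finding of no difference would then say nothing about whether the message works on first-line prescribing.

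**Working it through.** **1. When the list closes.** The rule names a baseline followed by three further pre-intervention periods and four post-intervention periods: 1 + 3 + 4 = 8. The outcome section gives four quarters before and four after: 4 + 4 = 8. The two agree, so baseline is the first of the four pre-mailing quarters, about 12 to 9 months before the mailing.

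**2. What can change afterwards.** The operations stated for the seven later periods are removal for death or out-migration and removal for change of provider. Neither adds a patient, and no replicate is exempted.

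**3. The rule against each population.**

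| Replicate | Population (Table 2) | Target behaviour | Can the closed list show an effect on it after the mailing? |
|---|---|---|---|
| 1 | Prevalent diabetes, 65 and over | Ongoing drug treatment | Yes |
| 2 | Incident diabetes, over 30 | Eye examination | Partly: listed patients can still be examined, but cases diagnosed after the first period never enter |
| 3 | New starters, 65 and over | Choice of initial drug | No: every listed patient started before the mailing |

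In replicate 2 the provider check raises a second difficulty. It needs prescriptions, and those data begin at age 65, so it cannot be applied to patients aged over 30 and under 65.

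**4. The plan's own power figure.** Inputs from the sample-size section: baseline 36%, intra-class correlation 0.092, 1,250 practices per arm, alpha 0.05 (two-sided assumed), 10 patients per practice, with 3 per practice also tested. Effective n per arm = 1,250 × m / [1 + (m − 1) × 0.092]. Power = Φ[(0.05 − 1.96 × SE0) / SE1], where SE0 is the pooled and SE1 the unpooled standard error.

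- m = 10: 12,500 / 1.828 = 6,838; power for 36% vs 41% is above 99.9%.
- m = 3: 3,750 / 1.184 = 3,167; power is 98.3%.

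The stated bound of more than 97% is reproduced. It does not depend on the cohort rule.

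**5. How many replicate 3 patients the rule would follow.** Practices: 2 × 1,250 + 4 × 625 = 5,000. The article does not give the period over which the 30,000 accrue, so even accrual over one or two years is assumed, with only the first quarter's starters followed. Power is for 36% vs 41%, borrowing the ACE-inhibitor baseline and correlation.

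| Case | Patients | Per practice | Effective n, 1,250 practices | Power, 1,250 vs 1,250 | Power, 1,250 vs 625 |
|---|---|---|---|---|---|
| All 30,000 | 30,000 | 6 | 7,500 / 1.46 = 5,137 | 99.9% | 98.9% |
| One-year accrual | 30,000 / 4 = 7,500 | 1.5 | 1,875 / 1.046 = 1,793 | 87% | 71% |
| Two-year accrual | 30,000 / 8 = 3,750 | 0.75 | 937.5 / 1 = 937.5 | 60% | 45% |

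In the last row the design effect is held at 1. The last two rows show only the loss of numbers. They suppose that a 5-point effect could appear in the followed patients, which for first-line choice it cannot.

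**The case against.** The best answer is that the article already has an entry rule elsewhere. The allocation section admits every attending patient who meets the criteria, by an algorithm specific to each gap, and Table 2 takes all new cases. The rule criticised here stands in a paragraph about losses, which aims to keep denominators accurate, and a condensed article may simply not repeat how new cases enter. Its language of assigned patients and plurality also resembles the sensitivity analysis in the allocation section, where each patient belongs to one provider, more than the main analysis, where a patient counts under every practice attended.

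This shows that the intention may have been sound. It does not remove the conflict. The denominator paragraph is not confined to a sensitivity analysis or to one replicate, and it describes every later period in terms of the initial patients. A programmer who followed it would build a closed cohort.

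Three stronger readings are tempting, and the document does not support them.

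- A reader might infer that the replicate 3 effect is zero by construction. The Table 2 outcome is receipt of a diuretic, which a later addition or switch can still move. What cannot be seen is an effect on the initial choice.
- A reader might infer that replicate 2 cannot work at all. A patient diagnosed before the mailing can be examined after it, and the four-quarter window is tied to prescribing-related interventions, so the scheme may not have been written for screening.
- A reader might infer that a null in replicate 3 would lead to printed messages being discouraged in general. The replicates are analysed separately and their differences discussed, and replicate 1 is not affected.

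**Conclusion.** The point holds as a conflict between two stated rules, and it is serious for replicate 3. Read literally, the denominator rule leaves no first-line choice made after the mailing in the replicate 3 analysis, so the effect that this replicate is designed to detect could not be observed. For replicate 2 the defect is smaller: later incident cases are left out, against Table 2, and the retention check is unusable under 65. Replicate 1 is sound.

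The conclusion for replicate 3 rests on the text alone and needs no numerical assumption. The patient counts do: 7,500 or 3,750 of 30,000 follow from one-year or two-year even accrual, neither of which the article states. Whether the rule was meant for the primary analysis of every replicate cannot be settled from the article, which is why the two sections must be reconciled.

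**What to change.** Reconcile the allocation section (with Table 2) and the section on loss to follow-up as follows.

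- **Replicate 1:** keep the closed list, and say that the rule applies to this replicate only.
- **Replicate 3:** form a new cohort of treatment starters in each period. Take post-mailing outcomes from patients who start after the mailing.
- **Replicate 2:** let incident cases enter by period. Check continued care by visits in the OHIP claims, which the plan already uses to link patients to physicians, in place of prescriptions.

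The cost is protocol wording and programming. The administrative data are already available to the investigators, and neither randomization nor the intervention changes.

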The Registered Persons Database (RPDB) identifies all persons in the province who are eligible for OHIP coverage. It will be used to link patient participants to the administrative databases, and to detect death and out-migration of patients over the course of the study. Claims from the ODB Program will be used to measure the prescribing changes that result from the interventions. These data are available only for people 65 years of age and older. Accordingly, the two drug-related replicates are restricted to that age group of the Ontario population. The ODB data are delivered to ICES within two weeks of the end of the month of the claim. Claims data from OHIP will be used to identify physician patient linkages, and to measure the delivery of ophthalmologic and optometric screening. All of these datasets are available at ICES, and all bear encrypted health card numbers that are unique to patients but common over time and across data sets.

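### Keeping patients after the mailing only if the study physician wrote the plurality of their prescriptions selects replicate 1 on the behaviour under test and cannot be computed under 65 in replicate 2

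*Protocol article*

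**What the plan says.** The section on recruitment, compliance, loss to follow-up and drop-out aims to keep the denominators of the outcome rates accurate. Deaths and out-migration are found in the RPDB. Change of provider is detected "the latter by a plurality rule for prescriptions". The rule runs over several periods: "For each of the succeeding observation periods (three pre- and four post-intervention"), initially assigned patients stay only if still eligible in the RPDB and if "the study physician must have written the plurality of the patient's prescriptions in that period". The section does not limit this to one replicate or to a sensitivity analysis.

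The section on allocating participants, with Table 2, defines things differently:

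- The main rule counts every eligible patient who attends the practice, and credits the practice with decisions made by any physician who saw that patient.
- A stricter assignment, by plurality of visits, is a sensitivity analysis. Only there, in a tie, "the patient will be assigned to the primary care physician who wrote the greatest number of their prescriptions during the study period".
- On prescription data: "Claims from the ODB Program will be used to measure the prescribing changes that result from the interventions". And: "These data are available only for people 65 years of age and older". Hence "the two drug-related replicates are restricted to that age group of the Ontario population".
- Replicate 2 studies "All incident cases of persons with diabetes, aged >30 years", with 100,000 patients expected and an eye examination as outcome.
- OHIP claims are named as the source for linking physicians and patients.

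**The concern.** In replicate 1 the primary outcomes are the percentages receiving an ACE inhibitor, two or more antihypertensives, and a lipid-lowering drug. A target prescription written by the study physician counts as a success and also helps the patient meet the plurality rule. A patient with no prescription in the period is a failure on every outcome, has no plurality prescriber, and leaves the denominator. Retention is therefore a post-randomisation event driven by the behaviour under test, and randomisation does not protect a comparison on the retained subset.

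In replicate 2 the rule calls for data that do not exist for part of the population. Applied literally, it would restrict a question about people over 30 to people of 65 and over.

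**Working it through.** **Inputs from the article.** Baseline ACE inhibitor rate 36%; ICC 0.092; 1,250 practices per arm with 10 patients each; a 5-point increase (36% to 41%) named as important; four post-mailing periods; ODB data from age 65; replicate 2 from above age 30.

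**The plan's own figure.** Design effect 1 + 9 × 0.092 = 1.828; effective n per arm 12,500 / 1.828 = 6,838. Two-sided power at 0.05 for 36% against 41% exceeds 99.9% (98.4% at three patients per practice), so the stated bound of more than 97% holds. Power is not the issue.

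**What selection does to the contrast.** Let r1 and r0 be the retention of patients with and without the outcome. Then

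observed rate = p·r1 / (p·r1 + (1 − p)·r0)

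observed OR = true OR × (r1 treated / r1 control) × (r0 control / r0 treated)

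The true OR for 36% against 41% is 1.235. Retention values here are assumptions.

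- Same retention in both arms (r1 0.90, r0 0.70 to 0.80): observed rates are 39–42% and 44–47%, the difference is 5.1–5.2 points, and the OR is still 1.235.
- r1 differing by arm (0.85 against 0.87, up to 0.80 against 0.90; r0 0.70 to 0.80): the difference is 5.6–8.1 points and the OR 1.26–1.39. With no true change in the rate, +0.5 to +2.8 points appear.

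A common selection thus raises the level but leaves the OR alone. The contrast moves when retention given the outcome differs by arm.

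**Can the mailing make it differ?** Simulation, 2,000,000 patients per scenario. Assumed: Poisson counts of non-target prescriptions from the study physician and from others; target drug from the study physician in 28% of patients and from another doctor in 8% (total 36%); others pooled as one prescriber; ties dropped. The effect column raises 28% to 33%. The shift column has 33% and 3%, so the total stays at 36%.

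| Mean count, study / other | No prescription | Retained with / without target drug | Control rate seen | True +5.0 seen as | Shift only seen as |
|---|---|---|---|---|---|
| 1 / 0.5 | 14.3% | 68% / 47% | 44.9% | 5.8 | +2.9 |
| 1.5 / 1 | 5.3% | 64% / 49% | 42.3% | 5.8 | +2.5 |
| 2 / 1 | 3.2% | 72% / 61% | 39.9% | 5.6 | +2.1 |
| 4 / 2 | 0.2% | 79% / 73% | 37.8% | 5.3 | +1.1 |

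For scale, with the planned numbers and no true difference, 1.96 × √(2 × 0.36 × 0.64 / 6,838) = 1.6 points.

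**Spill-over between outcomes.** With gamma-Poisson counts (study physician 1 to 3 per quarter, others 0.5 to 1, 80% of target drugs written by the study physician), an arm that raises lipid-drug use by 10 points and leaves ACE inhibitor use alone shows a false ACE change of −0.3 to −1.2 points. At 6 to 10 study-physician prescriptions per quarter this falls to about 0.2 points or less.

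**Replicate 2.** The age split is not given. If 40–80% of incident cases are under 65, the rule can be evaluated for only 60,000 down to 20,000 of the 100,000. Over 2 × 1,250 + 4 × 625 = 5,000 practices that is 12 down to 4 patients per practice, against 20 for the whole population.

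**Replicate 3.** Every patient has a new antihypertensive prescription and the outcome is which drug. The route by which untreated patients drop out is largely closed there, so the effect is weaker.

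**The case against.** **The rule may belong to the sensitivity analysis.** It speaks of assigned patients, and exclusive assignment appears elsewhere only as a sensitivity analysis. This reading is possible, but the section does not say so and presents the rule as how denominators are kept. What stands is that the two sections disagree and must be reconciled.

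**The effect estimate may hardly move.** This is largely right where retention depends on the outcome alike in all arms. A reader might infer from a 36% rate measured at 38–45% that the treatment effect is biased by a similar amount; the algebra above shows otherwise. With more prescriptions per patient the distortion shrinks. Differential retention remains plausible, because the mailing acts on the study physician's own prescribing.

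**Replicate 2 may be exempt.** The outcome measurement section ties four-quarter follow-up to mailings about prescribing, and the authors knew the ODB age limit. Against that, the retention rule names no exemption, and one year of follow-up is planned for each replicate. A reader might infer that everyone aged 31 to 64 will be lost. That follows only from literal application; what is certain is that the rule is undefined for them.

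**Two further inferences fail.** The intention-to-treat sentence in the same section concerns practitioners who leave the mailing list and promises nothing about patients, so the rule does not contradict it. The prescription tie-break is likewise undefined under 65, but matters only in the sensitivity analysis and only for patients tied on visits.

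**Conclusion.** The point holds in this limited form. As written, the rule conditions replicate 1's comparison on post-mailing prescribing, is undefined for replicate 2 patients aged 31 to 64, and conflicts with both the main patient definition and the visit-based sensitivity rule. Rates are inflated in all arms. Bias in the contrast requires retention given the outcome to differ by arm, for instance if prescribing moves to the study physician or another target drug changes. It is about 0 to 3 points in the scenarios examined, all of which rest on assumed prescription counts or retention. The documents establish neither its size nor that it will occur. In replicate 2 the number affected depends on an unstated age split and on whether the rule was meant to apply.

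**What to change.** Reconcile the section on allocating participants with the section on loss to follow-up, and drop the per-period prescription-plurality requirement from the primary analysis. Then:

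- Link patients to practices by OHIP visits, which can be used at all ages, from pre-mailing data where available.
- For newly incident or newly treated patients with no pre-mailing visit, use the visit at which they first meet the entry criteria.
- Keep each patient in that practice's allocated arm, and remove only deaths and out-migration identified in the RPDB.
- Keep the prescription-plurality rule as a sensitivity analysis for patients aged 65 and over.
- Use a visit-based tie-break in replicate 2's sensitivity assignment.

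The cost is rewording and a changed data-cut program; the trial already holds the data. The downside is some dilution from patients who change physician after the mailing.
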